## Abstract

**Background:**

Exacerbations of Chronic Obstructive Pulmonary Disease (COPD) are the main cause for hospitalisation. These hospitalisations result in a high pressure on hospital beds and high health care costs. Because of the increasing prevalence of COPD this will only become worse. Hospital at home is one of the alternatives that has been proved to be a safe alternative for hospitalisation in COPD. Most schemes are early assisted discharge schemes with specialised respiratory nurses providing care at home. Whether this type of service is cost-effective depends on the setting in which it is delivered and the way in which it is organised.

**Methods/Design:**

GO AHEAD (Assessment Of Going Home under Early Assisted Discharge) is a 3-months, randomised controlled, multi-centre clinical trial. Patients admitted to hospital for a COPD exacerbation are either discharged on the fourth day of admission and further treated at home, or receive usual inpatient hospital care. Home treatment is supervised by general nurses. Primary outcome is the effectiveness and cost effectiveness of an early assisted discharge intervention in comparison with usual inpatient hospital care for patients hospitalised with a COPD exacerbation. Secondary outcomes include effects on quality of life, primary informal caregiver burden and patient and primary caregiver satisfaction. Additionally, a discrete choice experiment is performed to provide insight in patient and informal caregiver preferences for different treatment characteristics. Measurements are performed on the first day of admission and 3 days, 7 days, 1 month and 3 months thereafter. Ethical approval has been obtained and the study has been registered.

**Discussion:**

This article describes the study protocol of the GO AHEAD study. Early assisted discharge could be an effective and cost-effective method to reduce length of hospital stay in the Netherlands which is beneficial for patients and society. If effectiveness and cost-effectiveness can be proven, implementation in the Dutch health care system should be considered.

**Trial registration:**

Netherlands Trial Register NTR1129.

## Background

Chronic Obstructive Pulmonary Disease (COPD) is a chronic disease that is currently ranked as fourth major cause of death globally [1]. Due to an aging population and late effects of smoking, the prevalence of COPD will increase in the following 20 years [2]. Projections for the year 2030 indicate that COPD will be third major cause of death, as a result of the projected increase of tobacco use, especially among women and low-and middle income countries [1]. COPD is characterised by an airflow limitation which is not fully reversible. Symptoms include sputum production, cough and dyspnoea. These symptoms are chronic and progressive over time [3].

Acute exacerbations of COPD can be defined as 'an event in the natural course of the disease characterized by a change in a patients' baseline dyspnoea, cough and/or sputum production that is beyond the day-to-day variations, is acute in onset, and may warrant a change in regular medication in a patient with underlying COPD' [3]. The exacerbation frequency is dependent on several factors including disease severity and number of exacerbations in the previous year [4,5]. Although most exacerbations are treated in the community [5], exacerbations are the main cause for hospitalisations in COPD patients [5,6]. Studies have shown that exacerbations and hospital admissions negatively influence patient outcomes, by increasing lung function decline [5,6], decreasing quality of life [7,8], increasing mortality [9] and increasing readmission risk [8,10].

With a mean length of stay in the hospital of 9 days [6,11] the large number of hospital admissions for exacerbations among COPD patients result in a high pressure on scarce hospital beds and high health care costs, accounting for up to 70% of total expenses for COPD [12,13]. Even without intervention, hospital costs will rise as a result of the increasing prevalence of COPD, especially among women. To reduce health care costs, alternatives for hospital treatment have been developed. One alternative that has gained popularity in the last 15 years are hospital at home schemes [14,15]. These schemes aim at reducing the pressure on hospital beds and overall health care costs without negatively influencing the patient outcomes and increase patient satisfaction [16].

### Hospital at home and early assisted discharge

Hospital at home is defined as "a service that provides active treatment by health care professionals in the patient's home for a condition that otherwise would require acute in-patient care, and always for a limited time period"[17]. Hospital at home is also known as 'home hospitalisation' or 'hospital in the home'. Depending on the target population of the scheme and the type of care provided, schemes vary in organisational structure and may involve different professionals [17]. Hospital at home schemes can be divided in admission avoidance schemes, (early) assisted or supported discharge schemes and combined schemes. Depending on who bears the financial and management responsibilities, the schemes can further be divided in community resourced or hospital resourced. Community resourced schemes commonly built on the existing infrastructure for care provision in the community, whereas hospital resourced schemes work on an outreach basis and home care is provided by hospital staff.

### Hospital at home for COPD exacerbations

Hospital at home schemes for the treatment of COPD exacerbations specifically, have been studied in several randomised controlled trials [18-25] and various non-randomised studies including observational studies [26-31] and studies with retrospective analysis [32]. Studies were performed in the United Kingdom [19,20,24-29,32], Ireland [30], Australia [23], Italy [18] and Spain [21,22,31]. These studies showed that approximately 25% of all patients with an acute exacerbation of COPD can be treated at home safely with no negative effects on their health outcomes and with great patient satisfaction [16]. These results triggered the wide implementation of hospital at home schemes for COPD exacerbations in the United Kingdom over the last 10 years [14,15]. In 2007, the British Thoracic Society developed the Hospital-at-Home in Chronic Obstructive Pulmonary Disease guideline providing a framework for the development and adjustment of hospital at home schemes [33].

Most hospital at home schemes active in the United Kingdom are assisted discharge schemes, with specialised respiratory nurses providing home care on an outpatient basis [14,15]. However, it remains unknown whether this is the most effective model for hospital at home care. The use of generic community district nurses or telephone monitoring might be an option that increases the capacity of the hospital at home schemes for COPD exacerbation. Supported by their positive results, Davison et al. [28] suggest that the use of generic community nurses in hospital at home schemes should be studied more intensively.

Hospital at home for COPD exacerbations initially requiring hospital admission has also been the subject of several cost or cost-effectiveness studies [18,22,23,25,34-36]. Significant and substantial cost savings were found in Australia (€1200 per episode) [23], Spain (€800) [22,35] and the United States (€1700) [37]. No significant cost savings were found for England and Italy [36]. (Amounts were converted to Euros, using exchange rates of March 2010). All studies were performed from a health care or payer perspective, meaning that they recorded only costs in the health care sector and not included costs of informal care. Although treating COPD exacerbations at home has the potential to reduce costs, whether and the extent to which it does so in the Netherlands is unknown. Apart from the exact organisation of the hospital at home scheme, its health economic impact depends heavily on national and local treatment patterns, health care delivery structures, funding and reimbursement systems, absolute and relative differences in unit costs of resource use and drug prices. The limited transferability of cost-effectiveness results to other settings stresses the need for setting-specific cost-effectiveness studies.

This contribution presents the design of the GO AHEAD trial (GO AHEAD is an acronym for Assessment Of Going Home under Early Assisted Discharge). In this Randomised Controlled Trial (RCT) patients admitted to the hospital for an exacerbation of their COPD are discharged early and monitored at home by nurses.

### Research questions

Our primary research question is: "What is the effectiveness and cost-effectiveness of an early assisted discharge intervention compared to hospital care as usual for patients hospitalised with an exacerbation of their COPD." The primary measure of effectiveness will expressed by the change in health status, measured by the change in Clinical COPD Questionnaire (CCQ) [38] scores between randomisation and day 7, while costs include COPD-related health care costs, patients' and informal caregivers' out-of-pocket costs and patients' and informal caregivers' costs of production loss.

The following secondary research questions will be addressed:

1) What is the long-term effectiveness of early assisted discharge compared to hospital care as usual?

2) What is the difference in treatment failures between the early assisted discharge scheme and usual care in hospital?

Treatment failure in the intervention group is defined as readmission before day 7 or death before day 7. In the control group treatment failure is defined as death before day 7 or clinical deterioration leading to prolongation of hospital stay after day 7.

3) What is the effect of early assisted discharge on readmission rates after discharge from hospital or the early assisted discharge scheme, in comparison with usual care in hospital?

4) What is the effect of early assisted discharge on mortality after discharge from hospital or early assisted discharge scheme, in comparison with usual care in hospital?

5) What is the effect of early assisted discharge on patients quality of life in comparison with usual care in hospital?

6) What is the effect of early assisted discharge on primary informal caregiver burden in comparison with usual care in hospital?

7) How is patient and primary informal caregiver satisfaction with the early assisted discharge scheme compared with usual care in hospital?

Additionally a discrete choice experiment (DCE) is performed in order to provide more insight in patient and primary informal caregiver preferences for different treatment characteristics.

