**Exclusion criteria:**

Major uncontrolled comorbidity

Mental disability

Active alcohol abuse and/or drug abuse

Inability to understand the program

Living outside care region of the home care organisation

Indication for admission to intensive care unit or non invasive ventilation

Insufficient availability of informal care at home

On day 1, all patients considered eligible for potential early discharge are invited to participate in the controlled clinical trial in which they either continue their hospital admission or are discharged early to home care. These patients are informed that, if they fulfil the in- and exclusion criteria and are still willing to participate on day 3, they will be randomised on day 3 and discharged on day 4. For patients admitted before 12:00 pm, the day of admission is considered as day 1, otherwise, the following day is considered as day 1.

Patients must have signed the informed consent form before randomisation on day 3, which means they have three days to decide whether they want to participate in the trial or not. This procedure is possible because the treatment in the first three days is not different from that of patients not participating in the trial. Data collected before the third day of admission will be destroyed if the patient does not give informed consent on that day. This procedure has been approved by the ethics committee.

Patients who refuse to participate in the trial are invited to participate only in the discrete choice experiment study without participating in the RCT. These patients are contacted by telephone one month after admission and asked to give informed consent for this part of the study. This informed consent form is different from the form that is used in the RCT.

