### Randomisation procedure

On the third day of admission clinical stability is assessed in order to determine whether patients can be randomised. This design for randomisation is adapted from the Spanish study performed by Diaz et al. [21] although the criteria for clinical stability were adapted to represent the current practice in the participating hospitals and because of the difference in treatment package patients receive at home. Patients need to meet the following criteria to be randomised: 1 acceptable general health defined as decrease of physical complaints, non dependency of therapies that can not be given at home and being able to visit the toilet independently; 2 normal or moderately increased blood sugar levels, defined as ≤ 15 mmol/L or ≥ 15 mmol/L while the patient is capable to regulate blood sugars independently at home; and respiratory complaints of dyspnoea, wheezing and rhonchi must have decreased in comparison with day one of admission. A special symptoms scoring list adapted from the one used by Ojoo et al [24] is used for this (see additional file 1: appendix 1). This scoring chart scores the major exacerbation symptoms such as dyspnoea, coughing, mucus production and colour and oedema. By scoring these symptoms daily, improvement or deterioration in comparison with the previous days becomes more visual and supports the pulmonologist when applying the randomisation criteria to the patient.

Randomisation is performed on a 1:1 scale using a computer-generated randomisation list that is placed in sealed envelopes containing the allocation sequence of the two treatment groups. Randomisation is performed per participating location of the hospitals. We chose this procedure to ensure all participating hospitals have a similar proportion of patients in the intervention group and patients in the control group and that the burden for each participating home care organisations is similar. Furthermore, a block size of 6 is applied to create equal numbers in both groups.

The treatment protocol for the following four days is started after randomisation and for the intervention group the process of discharge planning is started.

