On the fourth day of admission the intervention group is transferred home and undergoes the early assisted discharge intervention. The control group remains hospitalised and receives usual care in hospital.

In both groups, patient recovery progress is monitored daily using the translated and adapted exacerbation symptom scoring chart.

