### Early assisted discharge intervention

Patients randomised into the early assisted discharge group are transferred home on day four of admission. The previously described treatment is continued at home and supervised by nurses. These nurses have daily contact with the patient for four consecutive days. Main objective of the supervision of the home treatment is the observation of the patient's recovery and providing counselling and reassurance to the patient and the primary informal caregiver. The nurses also address medication compliance and inhalation techniques, provide support in applying breathing- and coughing techniques and, if applicable, provide support in adhering to dietary advices. If necessary patients, can be supported in their daily life activities (e.g. washing and dressing) by the home care organisation. During the four days of home treatment, the emphasis lies on the recovery of the exacerbation. Secondary objectives like disease management and smoking cessation are addressed during the first follow up moment one month after randomisation.

General practitioners are informed about patients' participation in the trial but are not directly involved in these patients' home care. In cases of deterioration of the patient, the patient is discussed with the treating hospital pulmonologist and if necessary the patient is readmitted to the hospital. Patients can contact the hospital 24 hours a day, 7 days a week with questions or in cases of emergency.

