### Data analysis

Data analysis will be performed according to the intention to treat principle. Data from patients who die, quit participation or are otherwise lost to follow up will be included in the analysis up until the point of drop out. Missing observations will be imputed or weighted appropriately.

All primary and secondary outcome measurements will be analysed using analysis of covariance. In order to control for dependency between the repeated measurements within one patient, and for the dependency between patients from the same hospital, multilevel analyses will be performed as well. We set the significance level at α = 0.05.

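### The intervention-arm failure definition has no non-fatal event for a patient who worsens after randomisation and is never sent home, although the same course counts as failure in the control arm

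*Protocol article*

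**What the plan says.** All references are to the protocol article.

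- **Timing.** Under Randomisation procedure: "On the third day of admission clinical stability is assessed in order to determine whether patients can be randomised". The recruitment text after the exclusion criteria tells patients that "they will be randomised on day 3 and discharged on day 4". After allocation, "for the intervention group the process of discharge planning is started". Under Early assisted discharge intervention: "Patients randomised into the early assisted discharge group are transferred home on day four of admission".
- **Failure, intervention arm** (Research questions, secondary question 2): "Treatment failure in the intervention group is defined as readmission before day 7 or death before day 7".
- **Failure, control arm** (same place): "In the control group treatment failure is defined as death before day 7 or clinical deterioration leading to prolongation of hospital stay after day 7".
- **Analysis set** (Data analysis): "Data analysis will be performed according to the intention to treat principle".

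Worsening in the intervention arm is discussed only for patients already at home, where the route is a return to hospital. The article does not say how to classify an allocated patient who worsens before transfer and stays in.

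**The concern.** Every intervention patient remains an inpatient for about a day after allocation. During that day the only non-fatal event that the arm can score, a readmission, is impossible. A patient who worsens then and is kept in hospital stays in the intervention denominator but can enter the numerator only by dying before day 7.

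The control definition has no such gap, because it counts worsening that extends the stay beyond day 7. Two patients with the same clinical course can therefore be scored differently because of allocation alone. Failure before day 7 is one of the outcomes on which the two strategies are compared directly, and events may be few, so one or two unscored patients could move the comparison. The direction is known in advance: it makes early discharge look better.

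**Working it through.** **Step 1. The plan's own figures.** The article gives no expected failure rate and no expected share of non-transfers. Its sample size is used here only to obtain the size of an arm, and it reproduces.

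- Preliminary calculation: difference 0.4, SD 1.04, two-sided 5%, power 80% gives 107 per arm, 214 in total, as stated.
- Revised calculation: pooled SD = √((0.988² + 0.922²)/2) = 0.956; residual SD = 0.956 × √(1 − 0.288²) = 0.915; f = 0.4/(2 × 0.915) = 0.219, stated as 0.22. The total is 164.1 at f = 0.22 and 166.3 at the unrounded f, against 165 stated.
- With 1:1 allocation, 165/2 = 82.5, or about 82 per arm.

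**Step 2. Apply both definitions to the same courses.** Each patient worsens between randomisation on day 3 and the planned transfer on day 4, and is kept in hospital.

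| Course after worsening | Intervention rule | Control rule |
|---|---|---|
| Survives, stay extended past day 7 | not a failure | failure |
| Dies before day 7 | failure | failure |
| Recovers and leaves hospital by day 7 | not a failure | not a failure |

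The arms differ only in the first row.

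**Step 3. Look for a correction elsewhere.** Secondary question 3 concerns readmissions after discharge, so it misses these patients too. The list of secondary outcomes names only the number of treatment failures. The economic evaluation records length of hospital admissions, so a long stay would be visible in the resource data, but nothing links it to the failure count.

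**Step 4. Size per patient.** 1/82 = 1.2 percentage points off the intervention failure rate; two patients 2.4 points; four patients 4.9 points.

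**Step 5. Illustration on assumed values.** Let p be the true failure risk by the control standard, equal in both arms. Let q be the share of the intervention arm that worsens before transfer, survives and stays past day 7. The counted intervention risk is p − q and the apparent risk ratio is (p − q)/p. Neither p nor q is in the article.

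| p | q = 1% (0.8 patients) | q = 2% (1.6 patients) | q = 5% (4.1 patients) |
|---|---|---|---|
| 5% | 0.80 | 0.60 | 0.00 |
| 10% | 0.90 | 0.80 | 0.50 |
| 15% | 0.93 | 0.87 | 0.67 |

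The right-hand column is an extreme. At p = 5% it places all failures before transfer, and at p = 10% half of them (5/10). If the first row of Step 2 were scored alike in both arms, every ratio in this table would be 1.

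**The case against.** The strongest case against is that this is a narrow gap in a secondary outcome, in a condensed article whose study-design figure is not available here.

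- **Few patients may be affected.** The window is about one day, and it follows a check requiring fewer complaints, eased respiratory symptoms and no reliance on treatment that cannot be given at home. This stands: the frequency is unknown and may be small. However, the check asks for improvement since day 1, not resolution, so later worsening is possible.
- **It may be detail left to the full protocol.** This does not stand. The article states an explicit definition for each arm, and the two definitions score one course differently.
- **It is part of a wider difference between the two definitions.** Partly right. Whether a readmission and an extended stay are comparable events is a separate question. Even if they were, patients never sent home could not have the first.

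A reader might infer that all early worsening disappears from the intervention arm alone. The documents do not support that: deaths before day 7 count in both arms, and worsening that resolves by day 7 counts in neither. A reader might also take the 1% to 10% readmission risks under Discrete Choice Experiment as expected trial rates. They are attribute levels shown to respondents, and they concern patients treated at home. They say nothing about failure before transfer.

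**Conclusion.** The concern holds in a limited form. An intervention patient who worsens after randomisation, is never transferred, stays past day 7 and survives is not a failure, while a control patient with that course is. This follows from the wording and the intention-to-treat statement and needs no assumption. The error can only favour early discharge.

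Its size cannot be derived from the article. The firm figure is about 1.2 percentage points per affected patient at 82 per arm. The risk ratios above rest on assumed values and on equal true risks in the two arms.

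It would go too far to say that the trial's main result is biased or that such patients are declared successes. The primary outcome is the CCQ change from day 3 to day 7, which does not use the failure definition. The sample size does not depend on it, mortality is a separate outcome, and the article defines no success category. The gap is still worth closing, because its direction is known and the repair is small.

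**What to change.** In secondary research question 2, state that failure is counted from randomisation in both arms. Add to the intervention-arm definition the non-fatal event that the control definition already contains, worsening that extends the hospital stay beyond day 7. A patient who is never transferred is then scored as a control patient would be. A patient readmitted before day 7 is already a failure and is unaffected.

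Record the reason for every non-transfer. Report organisational reasons, such as home care not being in place, separately and not as failures. Report non-transfers for worsening that resolves by day 7 as a sensitivity analysis. Counting these as failures in the main analysis would reverse the imbalance, because the control rule ignores the same course.

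The cost is one clause and one reason code; the data are already in the hospital record. The intervention failure rate may be slightly less favourable. Patient care, the primary analysis and the sample size do not change.

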#### Secondary outcome measurements

Main secondary outcome measurement of the study is the cost-effectiveness. This will be discussed in the economic evaluation section. The following other secondary measurements will be performed. These correspond with the secondary research questions from the last paragraph of the introduction:

1. Long-term effectiveness, measured with the CCQ change over the time points from day 1 to the end of the follow-up period (T4).

2. Number of treatment failures.

3. Number of readmissions to hospital and time to readmission during the three months follow-up period.

4. Mortality and time to death during the three months follow-up.

5. Generic health related quality of life, measured with the EuroQol (EQ-5D) 5D [41]. The EQ-5D will also be used to calculate quality adjusted life year (QALYs), discussed in the economic evaluation section.

6. Effects on primary informal caregiver burden measured by the Caregiver Strain Index [42].

7. Patient and primary informal caregiver satisfaction with the program. We use a translated version of the satisfaction questionnaire used by Ojoo et al. [24] and extended it with additional questions.

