#### Secondary outcomes measurements

All time-to-event outcomes (i.e. time to readmission and time to death) will be analysed using Kaplan-Meier curves and Cox Proportional Hazards regression model. Event rates (i.e. treatment failures, readmission rates and mortality rates) will be analysed using an appropriate model for count data (e.g. poisson regression or binomial regression)

Differences in outcomes defined as the mean change from baseline (e.g. long-term effectiveness, primary informal caregiver burden, patient- and primary informal caregiver satisfaction and quality of life) will be analysed using repeated measurements ANOVA.

Patient- and caregiver preference for place of treatment will be analysed using a logistic regression model.

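### Treatment failure is a different non-fatal event in each arm, so the planned comparison mixes treatment effect with definition

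*Protocol article*

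**What the plan says.** Secondary question 2, under Research questions, asks: "What is the difference in treatment failures between the early assisted discharge scheme and usual care in hospital". Two definitions follow. For early discharge: "Treatment failure in the intervention group is defined as readmission before day 7 or death before day 7". For usual care: "In the control group treatment failure is defined as death before day 7 or clinical deterioration leading to prolongation of hospital stay after day 7".

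The outcome list (Effect evaluation, Secondary outcome measurements) reduces this to one item, "Number of treatment failures". The analysis text (Data analysis, Secondary outcomes measurements) treats it as one quantity: "Event rates (i.e. treatment failures, readmission rates and mortality rates) will be analysed using an appropriate model for count data". The article gives no common definition and no mapping between the two.

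Two further places matter:
- The section on treatment for days 1-3 and 4-7 says "In both groups, patient recovery progress is monitored daily using the translated and adapted exacerbation symptom scoring chart".
- Question 3 asks "What is the effect of early assisted discharge on readmission rates after discharge from hospital or the early assisted discharge scheme", and question 4 sets the same starting point for mortality. The outcome list instead has "Mortality and time to death during the three months follow-up", with the same three-month window for readmission.

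**The concern.** The non-fatal parts of the two definitions differ in kind and in timing. The intervention event is a readmission with no stated cause, before day 7. The control event is a deterioration judged to have kept the patient in hospital after day 7. Two patients with the same clinical course can therefore be classified differently, and no regression model can separate that from a treatment effect, because the definition changes exactly where the treatment does.

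Failure, readmission and death are the outcomes in which harm from early discharge would show. A spurious difference could be read as harm, and a real one could be hidden.

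A related wording conflict affects readmission and death. Read literally, questions 3 and 4 start counting at the end of the hospital stay or of the home scheme, a time set after randomisation and possibly different by arm. The outcome list counts over the whole three months.

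**Working it through.** **The plan's own figures.** The article gives no failure rate, power or sample size for treatment failure. Its sample sizes concern the CCQ, and both reproduce:
- t-test: 2 × (1.96 + 0.842)² × 1.04² / 0.4² = 106.1, so 107 per arm and 214 in total.
- ANCOVA: average SD √((0.988² + 0.922²)/2) = 0.956. Multiplied by √(1 − 0.288²) this is 0.915. Then f = 0.4/(2 × 0.915) = 0.219, rounded to 0.22, which gives N = 165.

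They neither support nor weaken this point. They supply only the scale: 165/2 is about 82 per arm.

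**The same course under each definition.**

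| Course | Home arm | Control arm |
|---|---|---|
| Death before day 7 | Failure | Failure |
| Deteriorates on day 5; readmitted if at home; settled by day 7 | Failure | Not a failure |
| Deteriorates, needs care past day 7; if at home, managed there without readmission | Not a failure | Failure |
| Deteriorates on day 6; if at home, readmitted on day 7; if in hospital, stay prolonged past day 7 | Not a failure | Failure |

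The third row is possible because the Early assisted discharge intervention section makes readmission depend on need. The second row pushes the count up at home; the third and fourth push it up in hospital.

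**Expected ratio with no true difference.** Let the true deterioration rate be r in both arms, p the share of home deteriorations readmitted before day 7, and q the share of in-hospital deteriorations that settle by day 7. Leaving deaths aside, the counted rates are r·p and r·(1 − q), so the ratio is p/(1 − q). Equal deaths in both arms would pull it towards 1.

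**Illustration.** r, p and q are all assumptions. With r = 10% and 82 per arm, the expected counts are 82 × 0.10 × p and 82 × 0.10 × (1 − q). The last column is the exact probability that a two-sided pooled z-test at 0.05 rejects, used as a stand-in for the planned event-rate model.

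| p | q | Home | Control | Ratio | Chance of a significant difference |
|---|---|---|---|---|---|
| 1 | 0 | 8.2 | 8.2 | 1.0 | 0.049 |
| 1 | 0.25 | 8.2 | 6.15 | 1.33 | 0.084 |
| 1 | 0.50 | 8.2 | 4.1 | 2.0 | 0.216 |
| 1 | 0.75 | 8.2 | 2.05 | 4.0 | 0.502 |
| 0.50 | 0.50 | 4.1 | 4.1 | 1.0 | 0.042 |
| 0.75 | 0 | 6.15 | 8.2 | 0.75 | 0.084 |
| 0.50 | 0 | 4.1 | 8.2 | 0.5 | 0.216 |
| 0.25 | 0 | 2.05 | 8.2 | 0.25 | 0.502 |

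For r from 5% to 30%, the chance of a false difference is 0.057 to 0.192 when one definition counts 75% of the deteriorations and the other counts all of them. It is 0.115 to 0.644 at 50%, and 0.259 to 0.972 at 25%. With equal counting it stays at 0.042 to 0.051.

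**Questions 2 and 4 against the outcome list.** Take a control patient who dies in hospital on day 9 without having been discharged. The death is not before day 7 (question 2) and not after discharge (question 4), so as a death it falls under neither. The patient enters question 2 only if a deterioration had already prolonged the stay. A home patient who has completed the scheme and dies on day 9 is counted under question 4. Under the outcome list both deaths count.

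**The case against.** The strongest defence is that some arm-specific analogue is unavoidable. Controls stay in hospital and cannot be readmitted while there. Supervised treatment is planned for seven days in both arms, and both definitions express one idea: the patient needed more hospital care than planned because recovery failed. That explains the asymmetry, and it is why adding readmission to a shared definition would not cure it. It does not make the two sets of events equivalent, and a measure common to both arms exists in the daily chart.

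The article also condenses a fuller protocol, so adjudication rules may exist elsewhere. That is fair for procedure, but the definitions themselves are stated here.

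A reader might infer more than the text supports:
- *That the plan overstates failure in the home arm, for instance by a factor of two.* This requires every home deterioration to be readmitted before day 7. The article does not say so, and with p = q = 0.5 the ratio is exactly 1.
- *That the 10.5-day Dutch mean stay in the Discussion would turn most controls into failures.* That mean describes COPD inpatients generally, while trial patients had to be improving on day 3. A long stay counts only if deterioration caused it.
- *That this is the trial's main safety outcome.* The article lists it as one of seven numbered secondary outcomes.
- *That intention to treat is abandoned for readmission and death.* The Data analysis section states the principle, and the outcome list already uses the three-month window. Early deaths, and early readmissions in the home arm, also enter under question 2. What remains is a conflict of wording.

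A control patient discharged early and readmitted before day 7 has no readmission category, but that departs from the planned pathway and its frequency is unknown.

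**Conclusion.** The point holds as a defect of definition. Followed exactly, the plan compares two different non-fatal events as one rate and can show a difference, in either direction, when the arms deteriorate equally often. The ratio p/(1 − q) is the most that can be said about size. The ratios from 0.25 to 4.0 and the rejection probabilities above follow from assumed values of r, p and q and are not estimates for this trial. Confidence is high on the asymmetry; the documents leave the magnitude and direction of the bias open.

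Severity is moderate. The outcome is secondary, and neither the CCQ analysis nor N = 165 is touched. The wording of questions 3 and 4 is a smaller, separate inconsistency.

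**What to change.** 1. For the between-arm comparison, use one definition in both arms from randomisation to the end of day 7: death, or clinical deterioration by a single prespecified criterion on the symptom chart. Classify the charts without knowledge of arm where possible, and state how patients whose charting stops before day 7 are handled.
2. Report readmission (intervention) and stay prolonged by deterioration (control) descriptively, as separate arm-specific components and not as one tested rate.
3. Reword questions 3 and 4 to match the outcome list: readmission and death counted from randomisation to month 3 in all randomised patients.

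The cost is wording plus re-coding of existing charts and hospital records, with no additional patients. The chart is in an additional file and is described as support for the pulmonologist's judgement, with no threshold given in the article. A criterion therefore has to be chosen and fixed before any data are compared by arm, and the completeness of the charts needs checking.
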